### Management of Acute Pancreatitis

Patients will be managed by the local clinical team at each participating site based on the 2013 IAP/APA guidelines (7), and most clinical decisions will be left to them. All patients will receive initial standard treatment, including early enteral nutrition (start within 48 h after admission), routine medical treatment (antibiotics and sedatives as needed, organ support like mechanical ventilation, and vasopressors commenced at the discretion of the treating team. Patients with AKI (≥1.5x increase in creatinine above known baseline value) and meet predefined specific criteria described by Bellomo et al. (21) will be eligible for the introduction of RRT. Suspected infection of local pancreatic collections will be treated by the'step-up' approach, starting with percutaneous or transmural drainage followed by debridement using the preferred technique at each participating site.

### Endpoints

#### Primary Endpoint

The primary endpoint is plasma chloride concentration on the morning of day 3. The day 3 chloride will be the chloride measured in the morning bloods on the third day after enrollment, with the day of enrollment labeled day 1, the next day labeled day 2, and the following day labeled day 3. Thus, the measurement of day3 chloride will typically be 36–48 h from enrollment. The time point is chosen because high-rate intravenous fluid administration is expected during this period (initial 24–48 h), as early aggressive hydration is recommended in AP patients (23).

#### Secondary Endpoints Outcome Measures

##### Part I: Key Secondary Endpoints

MAKE 30 (Major Adverse Kidney Events by hospital discharge or day 30) and its components, including death, new receipt of RRT, or persistent renal dysfunction during the same time interval.

##### Part II: Clinical Points

Requirement of ICU admission during the index admission.Intensive care unit free and alive days to day 30.Hospital free and alive days to day 30.Ventilator free and alive days to day 30.Vasopressor free and alive days to day 30.RRT-free and alive days to day 30.New-onset organ dysfunction as judged by SOFA score [Time Frame: 30 days of enrollment].Daily SOFA score from day1 to day7.Daily SIRS score from day1 to day7.Daily assessment of abdominal pain (VAS score) from day1 to day7.Intravenous morphine equivalent dose from day1 to day7.Occurrence of infected pancreatic necrosis (IPN) during the index admission.Occurrence of sepsis during the index admission.Occurrence of intra-abdominal bleeding during the index admission.Occurrence of gastrointestinal fistula during the index admission.All-cause mortality during the index admission.Requirement of open surgery during the index admission.

##### Part III: Biochemical Endpoints

Highest creatinine in the first seven days.Highest serum chloride in the first seven days of enrollment.Daily serum chloride from day1 to day 7.Daily serum bicarbonate from day1 to day 7.Plasma NGAL concentration at day1, day2, day3, and day5.Healthcare resource use (hospital expenditure) during the index admission.

### Monitored Parameters and Data Collection

A web-based electronic database (Unimed Scientific, Wuxi, China) will be used for data collection and storage. All data are inputted by the nominated investigator at each participating site. Training for data entry was arranged by the provider for all nominated investigators by the CAPCTG coordinating center before study commencement. The data required to be collected during different phases are shown in Figure 2. The CAPCTG coordinating center will be responsible for data management, safety, privacy, and quality.

**Figure 2 F2:**
[figure not shown]
Schedule of enrollment, interventions, and assessments. MAKE denotes major adverse kidney events. PASS denotes pancreatitis activity scoring system.

### Statistical Analysis

The reporting and presentation of this trial will follow the CONSORT guidelines for stepped-wedge trials (24). Based on the principle of intention to treat (ITT), a full-analysis set (FAS) will be performed on the population with outcome reporting (day3 chloride concentration). FAS will be used for the analysis of baseline characteristics and main therapeutic interventions. The safety set (SS) will include all enrolled patients for assessing the safety profile of the intervention.

Descriptive statistics will be used to assess any marked baseline differences in demographics or outcome measures between the two groups, taking clustering into account. Comparisons of binary outcomes will be expressed as relative risk with 95% confidence intervals and comparisons of continuous outcomes as mean differences together with 95% confidence intervals. Between-group comparisons will be made using generalized linear mixed-model (GLMMs) with a hospital-level random effect to address clustering by hospital and random slopes of time to account for temporal effects, as delineated by Hussey and Hughes. Two-sided 5% significance levels will be used to identify statistically significant results. All confidence intervals reported will be 95% confidence intervals.

A series of subgroup analyses will be conducted for the evaluation of the primary endpoint: age (dichotomized at 60 years old), referral or non-referral, presence of AKI at enrollment, and presence of organ failure at enrollment.

For any possible missing data, we assume the data is missing at random while performing analyses by GLMM. Moreover, a series of sensitivity analyses after imputing the missing primary outcome using worse-case (i.e., values at baseline), Last Observation Carried Forward (LOCF), and multiply imputation will be used to validate and test the robustness of our trial result.

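### The full-analysis set is labelled intention-to-treat but admits only patients with a day-3 chloride, so the baseline table rests on a selected group and the planned imputations have no defined population

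*Protocol article*

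**What the plan says.** Everything at issue is in the Statistical Analysis section of the protocol article, which names two analysis sets.

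- **Full-analysis set.** It opens with "Based on the principle of intention to treat (ITT" and continues that "a full-analysis set (FAS) will be performed on the population with outcome reporting (day3 chloride concentration".
- **Its stated use.** "FAS will be used for the analysis of baseline characteristics and main therapeutic interventions".
- **Safety set.** "The safety set (SS) will include all enrolled patients for assessing the safety profile of the intervention".

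The last paragraph of the section deals with missing data. For the main model, "we assume the data is missing at random while performing analyses by GLMM". It then adds "sensitivity analyses after imputing the missing primary outcome using worse-case (i.e., values at baseline), Last Observation Carried Forward (LOCF), and multiply imputation". No set is named for these sensitivity analyses.

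The key secondary endpoint is "MAKE 30 (Major Adverse Kidney Events by hospital discharge or day 30) and its components, including death". Neither the endpoint sections nor the Statistical Analysis section says which set is used for it, or for the other clinical endpoints.

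**The concern.** Intention to treat means that membership of the analysis set is settled by enrollment and allocation. Here it is settled by something that happens afterwards and that the allocated fluid could influence: whether the patient is alive, in hospital and sampled on the third morning.

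Two consequences follow from the text as it stands.

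1. The baseline table describes only patients who reached the day-3 draw. In an open-label cluster trial, the baseline comparison of everyone enrolled is how a reader judges whether enrollment differed between the saline and balanced-crystalloid periods. A table restricted to later survivors with a sample cannot serve that purpose.
2. The definition does not fit the missing-data paragraph. A set defined by having the primary outcome contains no missing primary outcome.

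A third consequence is conditional. MAKE 30, all-cause mortality and the free-and-alive-days endpoints all count death. If they are analysed on this set, a death before the day-3 sample disappears as an event.

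**Working it through.** The plan gives no figure on this point to reproduce, so the check is mainly a comparison of statements.

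**Step 1. Who is outside the set?** The Primary Endpoint section puts the day-3 sample typically 36–48 h from enrollment. The descriptions of both fluid groups foresee that treatment within the seven-day window may end early through discharge or death. The Exclusion Criteria remove patients whose death is predicted within 24–48 h. That makes death before the draw less common, but it does not rule out unpredicted death, early discharge or a missed sample. Each such patient is enrolled and in the safety set, but outside the full-analysis set.

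**Step 2. What is left to impute?** Let N = 240 (Sample Size section) and let q be the proportion without a day-3 chloride. The documents give no q, so the values below are assumptions.

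- Set as written: N(1 − q) patients, of whom 0 have a missing primary outcome.
- Set of all enrolled patients: N patients, of whom Nq have a missing primary outcome.

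| Assumed q | Size as written | Missing in it | Size if all enrolled | Missing in it |
|---|---|---|---|---|
| 0% | 240 | 0 | 240 | 0 |
| 5% | 228 | 0 | 240 | 12 |
| 10% | 216 | 0 | 240 | 24 |
| 15% | 204 | 0 | 240 | 36 |
| 20% | 192 | 0 | 240 | 48 |

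The third column is zero for every q. Applied to the set as written, baseline-value imputation, last observation carried forward and multiple imputation all return the observed-case result.

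**Step 3. Is there another set for the imputations?** The only set holding every enrolled patient is the safety set, and its stated purpose is safety. No efficacy set contains the patients whose outcome would be imputed.

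**Step 4. What if MAKE 30 is analysed on this set?** If a group has MAKE 30 risk r and risk d of death before the draw, the risk seen in the set is (r − d)/(1 − d). All values here are assumed: r = 30% with saline and 27.5% with balanced crystalloid, a true difference of 2.5 points.

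- d = 2% in both groups: 28/98 = 28.6% versus 25.5/98 = 26.0%, a difference of 2.6 points.
- d = 2% with saline and 1% with balanced crystalloid: 28/98 = 28.6% versus 26.5/99 = 26.8%, a difference of 1.8 points.

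The contrast hardly moves when early death is equal and shrinks when it is lower with balanced crystalloid. If it were higher with balanced crystalloid, the formula would move the contrast the other way. The documents do not say which case applies.

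**The case against.** **The early deaths may not be lost from MAKE 30.** The text assigns the full-analysis set only to the baseline table and the treatment summary. The set for each secondary endpoint is a detail that an article may leave to the analysis plan. This stands. A reader might infer that deaths on day 1 or 2 are removed from MAKE 30 and mortality, or that most of a treatment effect would vanish. The documents support neither as fact: the first depends on an unstated choice, and the second needs nearly all of the effect to lie in deaths before the draw, in a population from which patients with predicted early death are excluded.

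**The imputations may be meant for all enrolled patients.** The text plans "a series of sensitivity analyses after imputing the missing primary outcome" without confining this to the full-analysis set. A coherent reading is that the main analysis uses observed values and the sensitivity analyses bring back the patients without one. This also stands as a reading, so it would be too strong to say that the imputation analyses are empty. But the text defines no efficacy set to which those patients belong, and the two paragraphs still need to be reconciled.

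**The missing-at-random assumption is not thereby false.** A mixed model of a single outcome fitted to observed cases is valid if missingness depends only on what is in the model. A reader might conclude that the stated assumption is not met; that does not follow. Using the day-1 and day-2 chlorides would allow missingness to depend on those values too, which is an improvement, not the correction of an error.

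None of this rescues the label or the baseline table. Both are stated outright, so neither is a detail left to another document.

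**Conclusion.** The point holds in this form. The article calls a set intention-to-treat while defining it by a post-enrollment outcome, and expressly bases the baseline table and treatment summary on it. It then plans imputations that would change nothing on that set, and it defines no other efficacy set for them. These conclusions rest on the wording alone and need no assumed rate.

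Loss of early deaths from MAKE 30, mortality and the free-and-alive-days endpoints is a risk that depends on whether this set is used for them. Its size and direction cannot be derived, because no early-death or missing rate is given. The counts of 12 to 48 excluded patients and the MAKE 30 contrasts in the working are illustrations under assumed rates, not estimates for this trial.

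**What to change.** 1. Define the full-analysis set as all enrolled eligible patients, analysed by the fluid assigned to their hospital on the admission date. This matches the allocation rule under Randomization Methods.
2. Use it for the baseline table, the treatment summary and all efficacy endpoints, naming MAKE 30, mortality and the free-and-alive-days endpoints explicitly.
3. Run the already planned imputation analyses of day-3 chloride on this set, with the multiple imputation drawing on the day-1 and day-2 chlorides.
4. Label the analysis of patients with a day-3 value as observed-case, not intention-to-treat.
5. State how a patient who dies before the draw is handled in the chloride analysis.

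The cost is wording in the analysis section. No new data are needed, since daily chloride from day 1 to day 7 is already among the biochemical endpoints.

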### Sample Size, Centers, and Recruitment

According to the previous study, the standard deviation of serum chlorine in patients with severe acute pancreatitis is conservatively estimated at 6mmol/L (22). A total of 240 patients will be recruited from 11 centers within 12 months (20 patients per month). They will provide 90% power to detect the serum chlorine difference of 1.5 mmol/L or more between the balanced crystalloid and the saline group on the basis of within period intra-class correlation coefficient (ICC) of 0.05 and cluster auto-correlation (CAC) of 0.5.

The starting date of patient recruitment was Apr 1^st^, 2021, and the planned finishing date is Mar 31^st^, 2022. The follow-up will be finished after the discharge of the last recruited patient.

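### The stated model omits the hospital-by-month variation that the sample size assumes; at 240 patients the effect on the primary endpoint is small

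*Protocol article*

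**What the plan says.** The Sample Size, Centers, and Recruitment section bases the calculation on a "within period intra-class correlation coefficient (ICC) of 0.05 and cluster auto-correlation (CAC) of 0.5", and on an SD for which "the standard deviation of serum chlorine in patients with severe acute pancreatitis is conservatively estimated at 6mmol/L". It plans the following recruitment: "A total of 240 patients will be recruited from 11 centers within 12 months (20 patients per month". Its power statement is: "They will provide 90% power to detect the serum chlorine difference of 1.5 mmol/L or more".

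Under Randomization Methods, all hospitals use saline in month 1 and one hospital changes over in each later month. That gives 11 sequences and 12 monthly periods.

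The Statistical Analysis section fixes the model: "Between-group comparisons will be made using generalized linear mixed-model (GLMMs) with a hospital-level random effect". The same sentence adds random slopes of time to deal with temporal effects. It names no hospital-by-period effect. On testing it says "Two-sided 5% significance levels will be used to identify statistically significant results", and it gives no reference distribution or degrees-of-freedom method.

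**The concern.** A cluster autocorrelation of 0.5 says that two patients in the same hospital but in different months are only half as correlated as two patients in the same hospital and month. The drop occurs at once, between any two months, however close. In a mixed model that is a random effect for each hospital-month.

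A random slope does something else. It lets each hospital drift along its own straight line, so adjacent months stay almost as correlated as the same month. It covers hospital-by-time variation only in part.

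In a stepped wedge, treatment is constant within a hospital-month. Variation at that level therefore feeds directly into the treatment contrast. If the model cannot represent it, the variation is treated as independent patient noise and the standard error comes out too small. At stake are the width of the confidence interval and the 5% level for the primary endpoint.

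**Working it through.** **Inputs.** K = 11 hospitals, T = 12 months, 240 patients, SD 6 (variance 36), ICC 0.05, CAC 0.5, difference 1.5 mmol/L, two-sided 5%. Patients per hospital-month: m = 240/(11 × 12) = 1.82. The calculations include fixed month effects, which is an assumption because the article does not say whether months also enter as fixed effects.

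**1. Implied variance components.**
- Hospital: 0.05 × 0.5 × 36 = 0.9
- Hospital-by-month: 0.05 × (1 − 0.5) × 36 = 0.9
- Residual: 0.95 × 36 = 34.2

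**2. The plan's own figure.** With τ² the hospital variance and s² the remaining variance of a hospital-month mean, the treatment effect has

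Var = K s²(s² + Tτ²) / [(KU − W)s² + (U² + KTU − TW − KV)τ²].

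For this design U = 66 and V = W = 506, so KU − W = 220 and the second bracket is 1430.

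- At m = 1.82: s² = 0.9 + 34.2/1.82 = 19.71. Var = 11 × 19.71 × 30.51 / (220 × 19.71 + 1430 × 0.9) = 1.176, so SE = 1.085. Power = Φ(1.5/1.085 − 1.96) = 28%, not 90%.
- At m = 20 per hospital per month (2,640 patients): s² = 0.9 + 34.2/20 = 2.61, SE = 0.455, power 91%.

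The stated 90% is therefore not reproduced at 240 patients. That is a separate matter. It is relevant here because the number of patients per hospital-month decides how much the omitted term matters.

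**3. Effect of the omission alone.** If the data have the components in step 1 and the model has a hospital intercept only, the best-fitting values are τ² = 0.935 and residual variance 35.06 (found numerically). Then s² = 35.06/1.82 = 19.29 and the formula gives a reported SE of 1.077, against a true 1.085. The ratio is 0.993, and the type I error is 2[1 − Φ(1.96 × 0.993)] = 5.2%. With the random slope in the working model the figure is also 5.2%.

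| Patients per hospital-month | Reported/true SE (intercept only) | Type I error |
|---|---|---|
| 1.82 (planned total) | 0.993 | 5.2% |
| 5 | 0.963 | 5.9% |
| 10 | 0.915 | 7.3% |
| 20 | 0.833 | 10.3% |

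**4. Null simulations, REML, 240 patients, equal hospitals, 1,500 trials** (Monte Carlo standard error about √(0.07 × 0.93/1500) = 0.7 points).

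| Model | Mean SE / empirical SD | z test | t, 9 df |
|---|---|---|---|
| Hospital intercept | 1.095/1.180 = 0.93 | 6.8% | 3.7% |
| Intercept + slope (as stated) | 1.098/1.184 = 0.93 | 7.0% | 3.9% |
| Intercept + hospital-by-month | 1.122/1.176 = 0.95 | 6.7% | 3.5% |

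The slope model behaves like the intercept-only model, so the slope does not supply the missing term. The added term changes the z-test error by 0.3 points, which is within simulation error. The reference distribution changes it by about 3 points.

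**5. Unequal hospitals or a higher ICC (both assumed).** In 600 trials per scenario, the z-test error of the slope model against the model with the hospital-by-month term was:
- equal hospitals: 6.3% against 5.5%;
- one hospital supplying 40% of patients: 6.7% against 6.5%;
- ICC raised to 0.15: 8.3% against 5.7%.

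A separate set of 400 trials per scenario gave 5.3% against 4.5% (equal), 7.8% against 7.5% (one hospital at 40%), and 9.0% against 8.3% (40% and ICC 0.15). The Monte Carlo standard error is about 1 point for 600 trials and up to 1.5 points for 400.

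**The case against.** The strongest reply is that the mismatch hardly matters. The random slopes are a partial hospital-by-time term. With fewer than two patients per hospital-month, residual noise swamps the hospital-by-month variance. The omission alone costs 0.2 points of type I error, and the difference between the two models under z tests is within simulation error for equal hospitals. Most of the excess over 5% comes from a normal reference with 11 hospitals, and the article does not say that such a reference will be used. All of this stands, and it limits the size of the point. It does not remove the inconsistency: the model is stated, and it is not the structure on which the trial was sized.

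Three stronger readings are tempting, and the document does not support them.

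- **Daily endpoints.** For series such as "Daily serum chloride from day1 to day 7" and "Daily SOFA score from day1 to day7", a reader might infer that repeated values will be pooled without a patient term, with badly inflated error, or else tested day by day in dozens of 5% tests. The article does not say how these series are modelled, and the two readings exclude each other. The within-patient correlation needed to size the first is not given. The full protocol or SAP may settle the matter.
- **No small-sample correction.** A reader might infer that one has been ruled out. The article is silent on degrees of freedom, and silence in a condensed article does not show an error.
- **Strong imbalance between hospitals.** The Discussion says that the sponsor's hospital admits more than 800 AP cases a year. That counts all AP, not patients who meet the eligibility criteria, and no other hospital's volume is given. The 40% share is an assumption.

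**Conclusion.** The point holds in a limited form. The sample size assumes hospital-by-month variance equal to hospital variance (0.9 each). The stated analysis model has a hospital effect and linear slopes only, so the two sections disagree and standard errors can be slightly too small.

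For the primary endpoint at 240 patients, the omission alone gives about 5.2% type I error. If z tests are used, the total is about 6% to 7%. In the simulations it reaches 8% to 9% only with an assumed ICC of 0.15, three times the plan's value, and in one of the two sets with one hospital at an assumed 40% as well. It would reach about 10% with 20 patients per hospital-month, which is not the planned total. These figures rest on the plan's ICC, CAC and SD, on fixed month effects, and on equal hospital sizes except where stated.

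**What to change.** In the Statistical Analysis section, specify for the primary endpoint a linear mixed model with a random hospital effect and a random hospital-by-month effect, in place of the random slope or in addition to it. Fit it by REML with Kenward-Roger or Satterthwaite degrees of freedom, because there are only 11 hospitals. If the SAP already states this, the article's description should be brought into line with it.

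No data collection changes. Intervals become slightly wider: in the simulations the mean SE rises from 1.098 to 1.122, and a t reference on 9 df uses 2.26 in place of 1.96. The correction may be mildly conservative. With t on 9 df the simulated error was about 3.5% for equal hospitals.

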### Randomization Methods

We used a computer-generated randomization scheme to determine the order in which each participating site crosses over from the control phase to the intervention phase. According to the stepped wedge design, all sites will initiate recruitment using NS for fluid therapy in the first month. Every month thereafter, one hospital will be randomized to use balanced crystalloids without a transition period. The assignment of patients will depend on their admission date (Figure 1).

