## Discussion

The best crystalloid for the early resuscitation of patients with AP remains controversial. The CLEVER-AP trial will, for the first time, provide evidence regarding the effects of normal saline and balanced crystalloid fluid on plasma chloride concentration and AKI in patients with pSAP. The findings of this trial will have direct clinical consequences as it will provide definitive evidence.

MAKE30 is identified as a key clinical endpoint, and it has been used successfully in several fluid trials (12, 25). MAKE30 is the composite of death, new RRT, or persistent renal dysfunction (PRD), which is recommended by the National Institute of Diabetes and Digestive and Kidney Diseases (NIDDK) workgroup for capturing effects of the short-term or longer-term evolution of AKI (26, 27). As such, it is a patient-centered and highly relevant endpoint for clinical research. Adopting MAKE30 as a key secondary endpoint will allow comparison with other major trials conducted with different patient populations.

The stepped-wedge cluster randomized design is adopted for the CLEVER-AP trial based on both methodology and clinical merits it could provide. From the methodology perspective, it uses the hospital as the entity of randomization because this will minimize the risk of treatment contamination and could greatly reflect the real-life practice across each hospital compared to randomization at the patient or physician level. Moreover, this design could model and assess the underlying temporal trends of the intervention with all hospitals accessing the intervention at the end of the rollout period. From the clinical perspective, since massive intravenous fluid infusion is essential and crucial in managing early acute pancreatitis, randomization at the patient level would make the intervention (fluid infusion with different types of crystalloids) vulnerable to misuse, potentially leading to contamination (12, 28). Moreover, the routine consent-and-randomization process in patient-level randomized trials takes a lot of time, during which no one knows what fluid should be used before randomization. Therefore, intravenous fluid before randomization, which could be massive, could significantly confound the trial results.

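### The primary model writes no fixed calendar-time effect: it assigns time to random slopes, yet cites a method built on fixed period effects

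*Protocol article*

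**What the plan says.** The Statistical Analysis section of the protocol article specifies generalized linear mixed models with "a hospital-level random effect to address clustering by hospital and random slopes of time to account for temporal effects", and closes the sentence with "as delineated by Hussey and Hughes". No other term for calendar time is named. Testing is at the two-sided 5% level.

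Under Randomization Methods, "all sites will initiate recruitment using NS for fluid therapy in the first month", and then "Every month thereafter, one hospital will be randomized to use balanced crystalloids without a transition period". With 11 hospitals this gives 12 monthly periods: none of the 11 hospitals is on balanced crystalloid in month 1, and all 11 are in month 12.

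The Discussion gives as one reason for the design that "this design could model and assess the underlying temporal trends of the intervention".

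**The concern.** In a stepped wedge, treatment and calendar time move together by construction. The usual protection is a fixed effect for each period, which estimates the trend shared by all hospitals. A random slope has mean zero: it describes how hospitals differ around a shared trend and does not estimate that trend. If the slope is the only time term, part of any shared drift in day-3 chloride (for example from case mix, referral timing, fluid practice, season or laboratory calibration) is attributed to the fluid.

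The sentence also points two ways. An analyst who follows its words fits random slopes; one who follows its citation fits fixed periods with a random intercept. The two models can give different primary estimates, and the choice should not be open once the data are visible.

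**Working it through.** **Inputs from the article (Sample Size, Centers, and Recruitment; Randomization Methods).** 240 patients, 11 hospitals, 12 months; SD 6 mmol/L; within-period ICC 0.05; CAC 0.5; target difference 1.5 mmol/L; one hospital crossing per month.

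**Assumption, not in the documents.** A common linear drift of total size L over the 12 months and no true treatment effect. L is taken as 1 to 3 mmol/L.

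**Variance components**
- Hospital: 36 × 0.05 × 0.5 = 0.9
- Hospital-by-period: 36 × 0.05 × 0.5 = 0.9
- Residual: 36 × 0.95 = 34.2
- Patients per hospital-month: 240 / (11 × 12) = 1.82
- Variance of a hospital-month mean, given the hospital effect: 0.9 + 34.2/1.82 = about 19.7

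**The plan's own figure.** With fixed period effects the generalized least squares (GLS) standard error of the treatment effect is 1.085, so power is Φ(1.5/1.085 − 1.96) = Φ(−0.58) = 28%. With no time term and no random slope the standard error is 0.814 and power is Φ(1.5/0.814 − 1.96) = Φ(−0.12) = 45%. Neither reproduces the stated 90%. About 91% appears, with period effects, only if 20 patients is read as per hospital per month (20 × 11 × 12 = 2,640). That is a separate matter, and the power statement does not settle which time term was intended.

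**Hand check of the confounding.** Put calendar time on a scale from 0 (month 1) to 1 (month 12). In the month at position k/11, k hospitals are treated and 11 − k are not, giving 66 hospital-months on each fluid.
- Mean position, treated: Σk²/(11 × 66) = 506/726 = 0.697
- Mean position, saline: Σk(11 − k)/(11 × 66) = 220/726 = 0.303

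A plain comparison of means would therefore pick up 0.697 − 0.303 = 0.39 of L.

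**GLS bias of the model as written.** Let V = 19.7·I + 0.9·J + σ²ₛ·tt′, where σₛ is the SD of the hospital slopes and t is centred time. Let Z hold an intercept and treatment only. The bias is the treatment element of (ΣZ′V⁻¹Z)⁻¹ ΣZ′V⁻¹d, where d is the drift.

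| SD of hospital slopes, per month | Over the year (× 11) | Share of L in the treatment estimate |
|---|---|---|
| 0 | 0 | 0.437 |
| 0.182 | 2.0 | 0.389 |
| 0.273 | 3.0 | 0.342 |
| 0.364 | 4.0 | 0.293 |
| 0.545 | 6.0 | 0.207 |

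For slope SDs up to 3 mmol/L over the year, the bias runs from 0.342 × 1.5 = 0.51 to 0.437 × 3 = 1.31 mmol/L. At the largest spread shown it is 0.207 × 1.5 = 0.31 to 0.207 × 3 = 0.62. With a fixed linear or categorical time term it is exactly 0 for a linear drift.

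**Simulated mixed-model fits, no true effect (200 to 400 data sets per setting, several implementations)**

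| Model | Drift L | Size of bias | Rejection |
|---|---|---|---|
| Random slopes, no fixed time | 0 | 0.06 | 5% |
| | 1 | 0.42 | 9% |
| | 1.5 | 0.50 to 0.56 | 8% to 9% |
| | 2 | 0.90 | 21% |
| | 3 | 1.06 to 1.27 | 18% to 35% |
| Fixed monthly periods | 0 to 3 | within about 0.12 of zero | about 4% to 9% |
| Fixed linear time plus random slopes | 1.5 and 3 | within about 0.1 of zero | about 5% |

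In some implementations 1% to 17% of fits failed and were dropped, and rejection rates there carry a Monte Carlo error of 2 to 3 points. A further run with fixed periods and random effects for hospital and hospital-by-period rejected 8.3% (Monte Carlo error about 1.6 points) with Wald tests. The 11 clusters therefore need a small-sample method.

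**The case against.** The strongest reply is that the article never rules out a fixed time effect. It cites a method that has one, and its Discussion expects temporal trends to be modelled. Random slopes are also usually fitted around a fixed mean slope, and under that reading the bias disappears in the simulations. A condensed article may leave the full list of fixed terms to an analysis plan that is not shown. All of this stands. A reader might infer that the trial will be analysed without period effects; the documents do not support that.

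Three further inferences also go too far.
- *That the whole of any trend is credited to the fluid.* Under half is, because hospitals on different fluids are compared within the same month and the slopes absorb some of the drift.
- *That the smaller standard error is a second, separate fault.* With no drift the slopes-only model rejected at 5%, so its standard error is calibrated in that case. The excess rejection comes with the bias.
- *That fixed periods would bring the analysis into line with the sample-size model.* The sample-size section states no period effects.

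What the reply does not answer is that the article does say which term handles temporal effects, names a term that cannot estimate a shared trend, and attributes it to a method that is specified differently. That is a conflict in the text, not a detail left for later.

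**Conclusion.** The point holds as a contradictory and incomplete specification of the primary model. If the sentence is followed literally, roughly 0.2 to 0.44 of a common linear drift enters the treatment estimate. A chloride level that falls over the year would look like a benefit of balanced crystalloid, and a rising one would hide it. The biases calculated above for drifts of 1.5 to 3 mmol/L are large enough, against the 1.5 mmol/L target, to change the primary conclusion.

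The size rests on three assumptions: the literal reading, a linear drift common to all hospitals, and the article's SD, ICC and CAC. Whether a drift of that size will occur is unknown. The bias fractions agree well across methods. The false-positive rates vary more and should be quoted only as a range.

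**What to change.** Replace the model sentence with one that names every time term, for example: *Day-3 chloride will be analysed with a linear mixed model with a fixed treatment effect, a fixed categorical effect of calendar month of admission, and random effects for hospital and hospital-by-month, using a small-sample correction suited to 11 clusters (such as Kenward-Roger).* Random time slopes may be kept in addition to the fixed time effect, for example as a sensitivity analysis, but not in its place. The method citation should then match the model.

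At about 1.8 patients per hospital-month, and for sparse binary outcomes in particular, a coarser fixed term (quarters) or a fixed linear term is a defensible alternative if named in advance. A linear term protects only against linear drift.

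The cost is one sentence before database lock and a wider interval. The standard error goes from about 0.81 to about 1.09, so the 95% half-width goes from 1.96 × 0.814 = 1.60 to 1.96 × 1.085 = 2.13 mmol/L, before any small-sample correction.
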